#### Sample Size Calculation

Patient participants will be grouped into 1 of 4 arms (as determined by the unit they were discharged from) in both the baseline (pre-intervention) and postintervention periods. Our primary outcome, CTM-3, is scored as a continuous variable (0 to 100%) based on a published algorithm [77]. THP pilot data with 107 patients showed a baseline CTM-3 score of 74% (SD 21.4; unpublished). Our sample size calculation is based on an anticipated 13% to 14% increase in CTM-3 score and a standard deviation of 21.4 (derived from our previous studies of Care Connector). To ensure analysis for each of the 8 subgroups to be significant, we required a higher sample size than would be required in typical drug trials where randomization occurs at the individual level. As such we will recruit 33 to 38 patients per group; 8 groups in baseline (264 to 304) and 8 groups in intervention (264 to 304) for a total of 528 to 608 (based on *P*=.05 and power of .80).

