#### Phase 2: Developmental Evaluation and Implementation Analysis

We will adopt a multimethod case study analysis approach [85], looking at within and between group assessments (Figure 4), accounting for hospital/service specific context variables. Single case and cross-case comparative analyses will be used to assess context, process, and outcome measures.

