**Figure 4 figure4:**
[figure not shown]
Within and between group pre-post analysis.

For quantitative outcome measures (eg, CTM-3, relational coordination, AQoL-4D), statistical comparisons between the pre- (baseline) and post- (intervention) data will be made using mixed-effects regression models to account for potential clustering effect of patients from the same service. As this is a complex intervention and local context/implementation factors may affect outcomes, we will perform sensitivity analysis and examine each of the participating services separately. For repeated measures within the same individual, we will use a difference in differences approach (eg, AQoL-4D measured at 0, 2 weeks, 1 month, and 6 months post-discharge). Patients may experience decline in QoL over time in both control and intervention groups for reasons unrelated to the intervention; a lesser magnitude of decline in intervention versus control group may suggest a benefit of the intervention.

For patients who do not complete a study follow-up, we will analyze all available data points. Additionally, understanding the characteristics (via collected demographic and administrative data of this study) of those who do not complete follow-up may inform us of under what conditions and for whom the technology works best.

Qualitative data will be analyzed using an ethnographic case study approach [86], adopting techniques such as interpretive descriptive coding methods and word tables [85] to support the within and cross case analysis as used in previous evaluations and similar case comparisons [33,48]. Two researchers trained in qualitative research will read interview and focus group transcripts and field notes, record key themes, compare, and discuss findings. Both inductive and deductive analysis techniques will be used to identify themes and then conceptually map with the CFIR theoretical framework. NVivo software (QSR International) will be used for qualitative data management.

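### Analysing each service separately cannot show that the CTM-3 effect differs between services; if four site-service pairs with the same true effect are judged by their own P values, a split verdict is likely

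*Protocol article*

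**What the plan says.** In the Phase 2 developmental evaluation and implementation analysis, the main quantitative method is a mixed-effects regression, used to allow for clustering of patients within a service. The next step is motivated by context: "As this is a complex intervention and local context/implementation factors may affect outcomes", and therefore "we will perform sensitivity analysis and examine each of the participating services separately". The opening paragraph of the same section adds: "Single case and cross-case comparative analyses will be used to assess context, process, and outcome measures".

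The Sample Size Calculation gives this reason for its numbers: "To ensure analysis for each of the 8 subgroups to be significant". It rests on an "anticipated 13% to 14% increase in CTM-3 score and a standard deviation of 21.4", and states that "we will recruit 33 to 38 patients per group; 8 groups in baseline (264 to 304) and 8 groups in intervention (264 to 304"), "based on *P*=.05 and power of .80".

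Study Design describes two sites and two services (acute medicine and rehab) with eight wards, half of them intervention. That is four site-service pairs, each with one intervention and one control ward. The effect is defined there as a difference in differences between ward groups and periods.

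**The concern.** If context modifies the effect, the effect differs between services. The method named for this is an analysis of each service on its own. A significant result in one service and a non-significant result in another is not evidence that the two differ, because the gap between them is never compared with its own standard error. This is a separate problem from false positives under multiple testing: services with exactly the same true effect can appear to differ.

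The sample size section makes the risk concrete, since it treats significance within each subgroup as the target, and outcome measures are among those to be compared across cases. With ethnographic material from every unit at hand, a plausible explanation can be found for almost any apparent difference. A service where Digital Bridge works as well as elsewhere could be described as one where local factors prevented it from working.

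**Working it through.** **Inputs.** From the Sample Size Calculation: effect 13 to 14 points on the 0 to 100 scale, SD 21.4, 33 to 38 patients per group and period, alpha 0.05, power 0.80. From Study Design: four site-service pairs and the difference-in-differences contrast. Assumptions made here: two-sided test, the increase read as absolute points, no clustering, the same true effect in every service, and each service judged by its own P value.

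**The plan's own figure.** For a comparison of two means, n per group = 2 × 21.4² × (1.96 + 0.84)² / δ². This gives 43 for 13 points and 37 for 14 points (44 and 38 with the t-test). One-sided, it gives 34 and 29. So 38 is recovered at 14 points two-sided, and 33 is only approached at 13 points one-sided (at n = 33 the one-sided detectable difference is 13.1 points). No single variant gives the whole range 33 to 38. All of these are two-mean comparisons, not differences in differences.

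**Standard error and power per service.**
- Difference in differences (four cell means): SE = 21.4 × √(4/n), which is 7.45 at n = 33 and 6.94 at n = 38.
- Pre-post in one intervention ward (two cell means): SE = 21.4 × √(2/n), which is 5.27 and 4.91.
- Power p = Φ(δ/SE − 1.96). Example: 13/7.45 − 1.96 = −0.215, so p = 0.415.

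**Chance of a split verdict.** With k services sharing one true effect, the chance that some but not all are significant is 1 − p^k − (1 − p)^k.

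| n per cell | Effect | Power, diff-in-diff | Split, 4 pairs | Power, pre-post | Split, 4 wards |
|---|---|---|---|---|---|
| 33 | 13 | 0.415 | 0.853 | 0.694 | 0.759 |
| 33 | 14 | 0.468 | 0.872 | 0.757 | 0.668 |
| 38 | 13 | 0.465 | 0.871 | 0.754 | 0.673 |
| 38 | 14 | 0.523 | 0.873 | 0.814 | 0.560 |

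All four pairs are significant in only 0.415⁴ = 3% to 0.523⁴ = 7.5% of trials under the difference in differences. At exactly 80% power per service the split is 1 − 0.8⁴ − 0.2⁴ = 0.589. Simulation (200,000 runs) of the lowest, highest and a middle setting agrees with the formula.

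**Size of the chance differences.** The median gap between the best and worst of four difference-in-differences estimates with one true effect is 13.7 (n = 38) to 14.7 points (n = 33), about the whole planned effect.

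**The other reading of service.** If only acute medicine versus rehab is meant, pooled over sites, each cell has 66 to 76 patients. Difference-in-differences power is 0.694 to 0.814 and the split is 2p(1 − p) = 0.303 to 0.425. Pre-post power is 0.937 to 0.981 and the split is 0.037 to 0.118.

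**Where the result stops holding.** With four services the split exceeds 50% only when power per service lies between 16% and 84%. At n = 38 that is a true effect of about 7 to 20 points for the difference in differences, or 5 to 14.5 points pre-post. With no true effect, at least one of four services is significant in the direction of benefit in about 10% of trials, or in either direction in about 19%.

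**The alternative.** In the same simulations a 3-df heterogeneity test across the four services signals a difference in about 5% of trials when there is none. Its sensitivity is limited: for 80% power, two site-services must differ by 2.80 × √2 × SE, which is 27.5 points at n = 38 and 29.5 at n = 33.

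**The case against.** The strongest defence is that the article is a condensed account. The separate analyses are presented alongside a sensitivity analysis, after a mixed model and a difference-in-differences design. The section also promises within- and between-group assessments that account for site and service context, and Figure 4, which may bear on this, is not shown. An interaction test may be in an analysis plan we do not have. That stands: the absence of such a test from the article is not the finding. What remains is what the text does fix, namely a method that cannot answer the question given as its reason, together with a sample size aimed at significance in each subgroup.

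Three stronger readings are tempting and are not supported.
- A reader might infer that the protocol will label services as responders or non-responders. No section states such a rule. The split-verdict figures show what happens if the P values are read that way.
- A reader might infer that chance alone will produce a split in most repetitions whatever the circumstances. This needs a common true effect near the planned size and four or more units. Study Design and Population and Recruitment use the word service for acute medicine and rehab; the crossed unit is called a site/service combination in Implementation Measures. Under the two-service reading a split is the less likely outcome.
- A reader might infer that the third research question and the scale-and-spread strategy would rest on this noise. Table 1 answers that question with interviews, focus groups, observation, documents, usability scores and system-use data. CTM-3 differences enter only through the cross-case comparison of outcomes.

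It is also fair that part of the 85% to 87% comes from sample sizes that give a difference in differences within one pair only 42% to 52% power. At 80% power the figure would still be 59%.

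**Conclusion.** The point holds in a conditional form. Separate analyses per service do not address whether context changes the effect, and one model with an interaction is a better method than the one stated. The consequence is large if services are the four site-service pairs read by their own P values (split in 85% to 87% of trials, or 56% to 76% pre-post) and moderate to small if two pooled services are meant (30% to 43%, or 4% to 12% pre-post). These figures assume a common effect of 13 to 14 points, SD 21.4, a two-sided 0.05 test and no clustering. Ward-by-period variation, left out here, would add further apparent differences. This should be corrected, but it does not threaten the primary comparison.

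**What to change.** State which unit is meant by service. Base any statement that the CTM-3 effect differs by service on one model of all wards with a service by ward-group by period interaction (3 df for four site-service pairs, 1 df for acute medicine versus rehab). Report service-specific estimates with 95% confidence intervals, and show these wherever the cross-case analysis discusses outcome differences. Label the separate-service analyses descriptive, and say that no service is classed as responding or not by its own P value. Shrinking the service estimates towards the pooled effect is optional.

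The cost is wording in the analysis plan; no extra patients or data are needed. The plan should also state the downside. The interaction test is weak (about 28 to 30 points between two site-services for 80% power). With one intervention and one control ward per pair, it cannot separate context from ward-by-period variation. Statements about context and CTM-3 will therefore be mostly descriptive.

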		**Patient (outcomes)**					
			Transition quality	CTM3^d^		1 to 2 weeks post-discharge	
			Health-related quality of life	AQoL-4D^e^		At 1 and 6 months post-discharge	
			Goal attainment	GAS^f^		As captured by ePRO^g^ (intervention only)	

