### Population and Recruitment

Patients will be recruited at the time of admission to one of the services (acute medicine or rehab) in the study. Patients aged 60 years and over, with CCN defined as presenting with 3 or more chronic conditions from the 16 most prominent in the population: arthritis (except rheumatoid arthritis), chronic coronary syndrome, dementia, hypertension, cardiac arrhythmia, rheumatoid arthritis, asthma, osteoporosis, stroke, depression, chronic obstructive pulmonary disease, acute myocardial infarction, diabetes, congestive heart failure, cancer, and renal failure.

This method is aligned with current and established methods to identify patients with CCN [67-69]. Patients must be slated to be discharged home. As the technology is only currently available in English, patients (or a caregiver) must be able to speak and read English. Patients with mild cognitive impairment will not be excluded if able to provide informed consent and engage with the intervention (independently or with caregiver aid). During phase 1, all recruited patients will receive usual care. During phase 2, recruited patients from the intervention wards will receive the Digital Bridge intervention while those from control wards will receive usual care. Family/caregivers of recruited patients may be invited to participate in qualitative interviews.

As workflow integration is a foundation for implementing technology, all hospital providers on the general medicine and rehabilitation services will be invited to participate. PCPs of recruited patients will be contacted and invited to participate while the patient is still in hospital. Recruited patients may still participate in the study if their PCP does not wish to participate or if they do not have a PCP at the time of study enrollment. Should the PCP choose to join, they will be consented and trained to adopt the technology to support their patients post-discharge if their patients were recruited from the intervention wards during phase 2.

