To determine cost-effectiveness in relation to outcome and process measures, an economic evaluation will be conducted to compare costs and outcomes among patients who transitioned out of hospital using Digital Bridge with the control patient group. Control and intervention patients will be followed for 1 year. Costs will be estimated from a societal perspective. Health services utilization and health system costs will be measured for 1 year using province-wide health system administrative data. Over 85% of total direct costs can be measured using a cost methodology for health administrative data implemented at ICES [76]. System utilization measures will include hospital admission, emergency department visits, days in acute care, 30-day readmissions, primary and specialty care visits, labs, diagnostic imaging, and 7-day post-discharge primary care follow-up. Out-of-pocket costs will be estimated using a patient survey. Caregiver time costs will be estimated using the average industrial wage. Total costs will include the sum of health system costs and out-of-pocket costs. Resources and costs required to design and implement Digital Bridge will be estimated through a project budget review.

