#### Phase 2: Economic Evaluation Analysis

A cost utility analysis will be conducted comparing total costs and quality-adjusted life years (QALYs) of Digital Bridge to usual care from the perspective of Canada’s health care system. Costs and utility values will be assessed over the study follow-up period. Analysis will conform to most recent Canadian guidelines for economic evaluation [89]. Responses to the AQoL-4D will be scored using preference weights, converting the 5 responses into a single summary index, where a score of 1 reflects perfect health and 0 is equivalent to dead [90]. QALYs will be estimated using total area under the curve methods [91]. Statistical analysis will be conducted in accordance with current guidelines for clinical and cost-effectiveness analysis alongside randomized controlled trials [92], accounting for the repeated nature of the cost and outcome data. The incremental cost and QALYs will be estimated using generalized estimating equations, a flexible multivariate regression framework that explicitly allows for the modeling of nonnormal distributional forms of repeated measure data. As we will have individual level data on costs and QALYs for the period of study follow-up, we will evaluate uncertainty of the cost utility estimates using nonparametric bootstrapping, obtaining 5000 estimates of costs and QALYs for each strategy. Bootstrapping results will also be used to estimate 95% confidence intervals and depict cost-effectiveness acceptability curves. These analyses represent the probability of an intervention being cost-effective to a range of potential threshold values that the health system may be willing to pay for an additional unit of effect. As a scenario analysis, we will also conduct a cost utility analysis from a societal perspective by including patient-related costs. Economic analysis will be conducted using Stata version 15.1 (StataCorp LLC) and Excel Visual Basic for Applications (Microsoft Corporation). Analyses will support a proposed model of scale and spread in the Ontario context and/or similar health system contexts in Canada based on patient volumes.

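### Table 1 collects AQoL-4D at two time points and the analysis uses four; if Table 1 governs, the within-person change has no pre-exposure value and the QALY area has no starting value

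*Protocol article*

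**What the plan says.** Table 1 of the protocol article, under patient outcomes, schedules the AQoL-4D "At 1 and 6 months post-discharge". It has no entry at recruitment, at discharge or at 2 weeks.

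The section on Phase 2 developmental evaluation and implementation analysis states: "For repeated measures within the same individual, we will use a difference in differences approach". Its example is "AQoL-4D measured at 0, 2 weeks, 1 month, and 6 months post-discharge". It then says how a result would be read: "a lesser magnitude of decline in intervention versus control group may suggest a benefit of the intervention". The same paragraph also names AQoL-4D among the outcomes compared between the baseline and intervention periods by mixed-effects models, and the Study Design section sets out a ward-by-period difference in differences.

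The Phase 2 economic evaluation section scores the AQoL-4D as a utility and states: "QALYs will be estimated using total area under the curve methods". On the period covered it says: "Costs and utility values will be assessed over the study follow-up period". The section on developmental and economic measures says: "Control and intervention patients will be followed for 1 year".

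On timing, Population and Recruitment says: "Patients will be recruited at the time of admission to one of the services (acute medicine or rehab) in the study". The Intervention section places the first components of the Digital Bridge before discharge, among them primary care access to Care Connector and the discharge summaries used for teaching.

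**The concern.** Two of the four AQoL-4D time points that the analysis relies on have no entry in the collection table. Both schedules are printed in full and disagree, so this is not a detail left out when an article was condensed. A site working from Table 1 would not collect the 0 and 2-week values, and they cannot be recovered afterwards.

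Health-related quality of life is named in the second research question and is a secondary outcome. It also supplies the effect side of the cost-utility analysis. If its first value comes at month 1, after the in-hospital and early post-discharge components have acted, a within-person change can miss or reverse an early benefit, and the utility curve has no origin.

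**Working it through.** The plan gives no effect size, power or QALY figure for the AQoL-4D, so there is no stated figure to reproduce. The check compares the schedules and then works through what each allows.

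**1. The schedules**

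| Time | Table 1 | Analysis section |
|---|---|---|
| Recruitment (before exposure) | no | not listed as such |
| 0 | no | yes |
| 2 weeks | no | yes |
| 1 month | yes | yes |
| 6 months | yes | yes |
| After 6 months, to 1 year | no | no |

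**2. Within-person change if Table 1 governs**

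Let d(t) be the intervention-minus-control difference in mean utility at month t. The group difference in within-person change from a to b is d(b) - d(a). Utility sizes below are assumed, because the documents give none.

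- *Effect e complete by month 1 and sustained, with no difference at time 0.* From 0 to 6 months: e - 0 = e. From 1 to 6 months: e - e = 0, whatever the value of e.
- *Effect of 0.06 at month 1 fading linearly to 0 at month 6.* From 1 to 6 months: 0 - 0.06 = -0.06, a steeper decline in the intervention group. From 0 to 6 months: 0 - 0 = 0. The QALY gain by the trapezoid rule is [1 x (0 + 0.06)/2 + 5 x (0.06 + 0)/2] / 12 = (0.03 + 0.15) / 12 = 0.015.

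Under the plan's rule that less decline suggests benefit, the second case would be read as harm.

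**3. QALY area if Table 1 governs**

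The segment from discharge to month 1 has no starting utility. It is 1/6 (17%) of a 6-month area or 1/12 (8%) of a 1-year area. Take an effect that builds linearly from 0 to e over month 1 and then holds. Over 6 months:

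- true area = (0.5e + 5e) / 12 = 5.5e/12
- observed part only (months 1 to 6) = 5e/12
- 1-month value carried back to discharge = 6e/12

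| Assumed e | True, 0-6 months | Months 1-6 only | Carried back |
|---|---|---|---|
| 0.03 | 0.0137 | 0.0125 | 0.0150 |
| 0.06 | 0.0275 | 0.0250 | 0.0300 |
| 0.10 | 0.0458 | 0.0417 | 0.0500 |

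Dropping the first month understates the gain by 0.5/5.5 = 9%; carrying back overstates it by the same 9%.

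**4. If the analysis section governs**

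A time-0 value exists and the area can be computed from it. As worded, however, all four times are counted from discharge, so the 0 value may follow in-hospital exposure. It would then not be a clean baseline for change or for adjustment.

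**5. The end of the horizon**

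The economic follow-up is 1 year, and neither schedule has a utility after month 6. Half of that year (6/12) has costs but no measured utility.

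**The case against.** The strongest reply is that the harm is conditional. If the analysis section is the operative schedule, a starting value exists and the first-month gap disappears. The label 0 might even mean enrolment, which takes place at admission. Figure 1 carries the data collection timelines and is not shown, so the operative schedule cannot be established. This stands as a limit on the consequence. It does not remove the contradiction, because no third statement can make both printed schedules true.

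A reader might infer that every AQoL-4D comparison is lost. The documents do not support that. The mixed-effects comparison of baseline and intervention periods, in control and intervention wards, uses levels in different patients. It works with 1- and 6-month values and would detect a constant gain at both.

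A reader might also infer a definite QALY bias from the nonrandomized choice of wards. For example, an assumed persistent utility imbalance of 0.05 gives 0.05 x 0.5 year = 0.025 QALY over 6 months with no true effect. That figure needs a 6-month horizon, which the plan does not set. It also needs a contrast of the intervention period alone, with neither baseline-utility adjustment nor the ward-by-period contrast. An imbalance that is stable across periods would cancel in the double difference. The economic section specifies neither safeguard but excludes neither, and covariates are commonly left to a fuller analysis plan. The size of any such bias cannot be derived from the documents.

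Finally, the AQoL-4D is a secondary outcome, and CTM-3 and its sample size are untouched. That is right and bears on the severity.

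**Conclusion.** The point holds as an internal contradiction with conditional consequences, and it should be fixed. The two AQoL-4D schedules disagree on two of four time points.

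If Table 1 is followed, the planned within-person change compares two post-exposure values. It returns 0 for any effect complete by month 1 and sustained, and a negative value for an early benefit that fades. The QALY area then lacks a starting value for 1/6 of a 6-month horizon or 1/12 of a 1-year horizon. The direction of these results is arithmetic; the utility sizes are assumed.

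If the analysis section is followed, the area has a start, but its time 0 may not precede exposure. Under either schedule the utility horizon stops at 6 months against 1 year of follow-up.

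It would go too far to say that the quality-of-life and QALY results are certainly wrongly anchored, or biased by a known amount.

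**What to change.** - Make Table 1 and the Phase 2 analysis section state one schedule: AQoL-4D at recruitment on the ward before any Digital Bridge exposure, at the existing 1-2 week CTM-3 contact, and at 1 and 6 months. The recruitment measurement should have the same timing in all wards and in both periods.
- Say what time 0 means.
- Adjust the AQoL-4D and QALY analyses for the recruitment value.
- State the QALY horizon. If it is 1 year, say how months 6 to 12 are handled; if it is 6 months, align the costs used in the cost-utility ratio with it.
- For patients already enrolled without a recruitment value, drop the within-person change analysis and rely on the ward-by-period interaction on 1- and 6-month levels, which the design already supports.

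The cost is an amendment to Table 1 and two brief questionnaires per patient. One is at recruitment, when an information sheet is already completed, and the other is at a contact that already exists.
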